## Abstract

**Background:**

In recent years it has become clear that fetal anomalies can already be detected at the end of the first trimester of pregnancy by two-dimensional (2D) ultrasound. This is why increasingly in developed countries the first trimester anomaly scan is being offered as part of standard care. We have developed a Virtual Reality (VR) approach to improve the diagnostic abilities of 2D ultrasound. Three-dimensional (3D) ultrasound datasets are used in VR assessment, enabling real depth perception and unique interaction. The aim of this study is to investigate whether first trimester 3D VR ultrasound is of additional value in terms of diagnostic accuracy for the detection of fetal anomalies. Health-related quality of life, cost-effectiveness and also the perspective of both patient and ultrasonographer on the 3D VR modality will be studied.

**Methods:**

Women in the first trimester of a high risk pregnancy for a fetus with a congenital anomaly are eligible for inclusion. This is a randomized controlled trial with two intervention arms. The control group receives ‘care as usual’: a second trimester 2D advanced ultrasound examination. The intervention group will undergo an additional first trimester 2D and 3D VR ultrasound examination. Following each examination participants will fill in validated questionnaires evaluating their quality of life and healthcare related expenses. Participants’ and ultrasonographers’ perspectives on the 3D VR ultrasound will be surveyed. The primary outcome will be the detection of fetal anomalies. The additional first trimester 3D VR ultrasound examination will be compared to ‘care as usual’. Neonatal or histopathological examinations are considered the gold standard for the detection of congenital anomalies. To reach statistical significance and 80% power with a detection rate of 65% for second trimester ultrasound examination and 70% for the combined detection of first trimester 3D VR and second trimester ultrasound examination, a sample size of 2800 participants is needed.

**Discussion:**

First trimester 3D VR detection of fetal anomalies may improve patients’ quality of life through reassurance or earlier identification of malformations. Results of this study will provide policymakers and healthcare professionals with the highest level of evidence for cost-effectiveness of first trimester ultrasound using a 3D VR approach.

**Trial registration:**

Dutch Trial Registration number NTR6309, date of registration 26 January 2017.

## Background

Congenital anomalies account for 15–20% of all fetal deaths and nearly 25% of all neonatal deaths in Europe [1]. Around 2% of all pregnancies are affected by a major anomaly that requires extensive postnatal support [2]. A correct prenatal diagnosis can direct future parents to the best possible care.

According to international and Dutch national guidelines, all pregnant women are offered a second trimester two-dimensional (2D) ultrasound scan to screen for fetal anomalies [3–5]. Subsequently, future parents are counseled about the possible diagnosis, prognosis and treatment. However, by the end of the first trimester (< 14 weeks gestational age (GA)), a considerable amount of fetal anomalies can already be detected using 2D ultrasound [6, 7]. A systematic review, performed in a high risk population, showed that 61% of the (detectable) anomalies can already be identified by a first trimester anomaly scan [6]. A more recent prospective cohort study performed in The Netherlands even found a detection rate of 63% within a low risk population, which demonstrates the importance of performing a first trimester anomaly scan [8]. The observed high detection rate of major anomalies and ultrasonographic markers coincides with other advantages. Firstly, detection of an anomaly at an early stage in pregnancy provides additional time for counseling, advanced genetic testing, parental thought and reflection [9]. Secondly, a first trimester scan showing no abnormalities might provide parental reassurance, especially in a population at higher risk of fetal anomalies. Thirdly, if applicable, an early termination of pregnancy is considered a low risk procedure, in contrast to termination during advanced gestation, which shows a greater risk of maternal morbidity and mortality [10, 11]. When pregnant women opt for an early termination of pregnancy, methods available are considered less invasive when compared to termination at an advanced stage. Moreover, it has been shown that termination of pregnancy at a more advanced gestational age is associated with an increased risk of an adverse psychological outcome [12].

Finally, women with an increased BMI (i.e. > 30 kg/m^2^) could profit from a first trimester anomaly scan. It is known that the performance of the second trimester transabdominal ultrasound examination in women with an increased BMI is limited with regards to detection and completeness [13]. Incomplete ultrasound examination may lead to suboptimal care for these women. The efforts and costs greater when compared to women with a BMI < 30 kg/m^2^. In the first trimester, transvaginal ultrasound may be used to overcome limited visibility in the women with an increased BMI.

From the above mentioned, we can conclude that postponing detection of anomalies to the second trimester of pregnancy can be regarded as a missed opportunity. This is the most compelling argument mentioned in international guidelines proposing a first trimester anomaly scan to be offered to all women, accompanied by adequate counseling of the potential benefits and limitations [14]. However, there is a lack of implementation of the guidelines’ advice in nationwide screening programs. The available literature concerning detection rates and feasibility of the first trimester anomaly scan include a low risk population and are retrospective in design [6]. Prospective or randomized trials for a high risk population are limited in number. In spite of this, some countries are offering a first trimester anomaly scan to their population [15].

Over the years several factors have contributed to the quality of first trimester 2D ultrasound imaging. The most important ones are the introduction of high frequency ultrasound probes and using the transvaginal approach. The addition of an application providing three-dimensional (3D) renderings have further enhanced first trimester ultrasound imaging by enabling improved visualization of fetal structures [16]. However, there are also limitations concerning 3D ultrasound examinations. The 3D datasets are presented as 3D reconstructions on 2D screens. Therefore, the third dimension, depth, cannot be used to its fullest since the images are being presented on 2D media. Improved visualization can be reached using Virtual Reality (VR) displays. VR enables true depth perception and provides 3D interaction. ‘Holograms’ of the 3D ultrasound scans can be created using the V-Scope software (Erasmus MC, Rotterdam, The Netherlands), allowing presentation of volumetric data in the best possible way [17, 18]. Following the acquisition of 3D data, using any 3D probe, application of V-scope imaging software enables 3D data to be displayed as ‘holograms’ on a 3D display, generating depth perception using 3D glasses. The difference between 2D, 3D and 3D VR is depicted in Fig. 1. These generated ‘holograms’, show easier to interpret images and provide detailed and relevant information about the fetal anatomy [19]. 3D VR might improve antenatal counseling of future parents.

**Fig. 1 Fig1:**
[figure not shown]
Different imaging techniques of the same pregnancy in the first trimester. Images, representing respectively transvaginal two-dimensional (panel **a**), three-dimensional (panel **b**) and three-dimensional virtual reality (Panel **c**) ultrasound images of the same pregnancy in the first trimester

The VR technology has already been used extensively to visualize 3D ultrasound datasets in the Barco I-Space system; which is a special room enabling VR [16]. To facilitate clinical use, a 3D VR Desktop system has been developed (Fig. 2 – photo published with consent of future parents and examiner). This system can be used in daily outpatient practice, offering the same functionality at a fraction of the cost [17, 18]. Baken et al. have compared 2D ultrasound, 3D ultrasound and 3D VR for detection of first trimester fetal anomalies [20]. This retrospective study showed that the general diagnostic performance between the different methods was comparable (sensitivity 3D: 52.2%, 3D VR 62.6%; specificity 3D: 99.7%, 3D VR 99.6%). 3D VR has shown to be of additional value in the detection of anomalies, especially with regards to limb defects, conjoined twins and aneuploidy [21, 22]. Besides improving visualization, V-Scope enables the measurement of regularly used biometric features (e.g. crown-rump length) and more recently developed biometric and volumetric features (e.g. embryonic volume) with high reproducibility [23–27]. There is no difference with regards to the measurements performed in the I-Space or 3D VR Desktop system (excellent inter- and intra-observer class correlation (> 0.99)) [18].

## Methods/design

### Primary study objective

The general aim is to study the detection rate of a first trimester anomaly scan using 3D VR ultrasound in addition to the second trimester 2D ultrasound examination in a high risk population.

### Secondary study objectives

Additionally, we will investigate quality of life as reflected by psychological burden, and cost-effectiveness of the first trimester 3D VR ultrasound. Both factors will be compared between the intervention and control group. Finally, patient and ultrasonographer perspectives will be studied.

### Study design (see Fig. 3)

The design is a randomized controlled trial amongst women with a high risk for fetal anomalies in their pregnancy. Participants will be allocated to either the control or intervention group. In the control group, participants will receive ‘care as usual’ according to the Dutch national guidelines. The intervention group will undergo an additional first trimester 2D and 3D VR ultrasound examination. Both groups will be asked to complete questionnaires on wellbeing, quality of life, stress, anxiety and medical costs.

**Fig. 3 Fig3:**
[figure not shown]
Flow chart depicting the design of the VR FETUS Study. Flowchart showing the study design of the study; including the inclusion criteria, the usual care, the intervention arm, the control arm and the follow-up. GA: Gestational Age. 2D: two dimensional. US: Ultrasound. 3D: three dimensional

### Study population

Women with an increased risk of carrying a fetus with a congenital anomaly (i.e. high risk) are eligible for participation. Women are considered high risk when: they have a previous child with an anomaly or one of the future parents has an anomaly, there is a second or third degree family member (of the fetus) with a neural tube defect, there is a maternal disease (such as diabetes or auto-immune disease), the pregnancy is conceived after IntraCytoplasmic Sperm Injection (ICSI), following teratogenic maternal medication or substance use or when there is a monochorionic twin pregnancy.

They have to meet the following additional criteria:
18 years of age and olderWithin the first trimester of pregnancy, up to 14 + 0 weeks’ gestationSingleton or twin pregnancySufficient understanding of the Dutch language

Excluded from participation are women with a non-viable pregnancy and an anomaly detected before randomization.

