### Procedures, recruitment and randomization

Eligible women will be identified by the participating hospital. Referring healthcare providers will be contacted to ensure timely referral (< 14 + 0 weeks’ GA). Women eligible for the trial will be counseled before participation by medical doctors or research nurses in accordance to the ‘Good Clinical Practice (GCP)’ guidelines [30]. Written informed consent will be obtained (Supplement 1 and 2).

Following participation, the participant will be entered in a web-based computerized database (ALEA®) for randomization. After complete registration in the online randomization database, the allocation will be shown. The online randomization software is available at all times. Randomization will be performed using block randomization with random block samples of *N* = 4–16. Due to the nature of the intervention, this will not be a blinded study.

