### Intervention group

The intervention consists of a first trimester 2D and 3D VR ultrasound examination between 11 and 14 weeks GA. The examination will be performed on a Voluson E10 (GE Healthcare, Austria) using a 4–9 MHz or 6–13 MHz high frequency transvaginal transducer or 2–6 MHz transabdominal transducer. A complete ultrasound examination will take 30–45 min per fetus. Ultrasound examinations will be performed according to international guidelines on safe use of ultrasound in the first trimester of pregnancy and as such, total scanning time will be kept as low as possible (ALARA-principle) [31].

The ultrasound examination will be performed by two examiners (examiner A and B) unable to see of each other’s results. Examiner A will perform the 2D ultrasound and (2D) evaluation of fetal organ structures using a protocol with standard anatomical views and measurements (Supplement 3). The cardiac examination, based on international ISUOG practice guidelines, is expanded with at least 7 measurements or planes: four chamber view with and without color Doppler, left outflow tract with color Doppler, right outflow tract with color Doppler, three vessel view, trachea view, tricuspid valve pulsed wave Doppler and a measurement of cardiac axis [32]. By default a transvaginal ultrasound examination will be performed. Only if fetal structures cannot be sufficiently visualized or if a women objects to a transvaginal examination, a transabdominal approach will be performed. During the 2D ultrasound examination, in addition to the already described 3D ultrasound datasets, four-dimensional spatio-temporal image correlation (4D STIC) datasets of the fetal heart will be acquired. Examiner B will evaluate the acquired 3D volumes using the 3D VR Desktop system [18]. Participants undergoing the first trimester scan will be unable to see the 2D scan. This is necessary to test their experience and objective reaction with respect to the 3D VR images. Thus, the influence of 3D VR ‘holograms’ on future parents’ perception can be investigated and compared to their 2D ultrasound experience later in pregnancy (at 20 weeks).

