### Questionnaires

All participants will fill out questionnaires on health related quality of life. The following validated questionnaires will be sent at fixed time points in pregnancy: the MOS 36-item Short Form Health Survey (SF-36), the Hospital Anxiety and Depression Scale (HADS), the Spielberger State-Trait Anxiety Inventory (STAI) and a visual analogue scale (VAS) for wellbeing [33–35]. The four questionnaires will be sent digitally to the participants on the day of inclusion, the first trimester 3D VR ultrasound (or after 13 weeks GA for the control group), the second trimester 2D ultrasound and 4 weeks after the estimated due date, respectively. The answers will be recorded on a secure webserver on the Erasmus MC premises.

Direct healthcare costs will be recorded using the iMTA Medical Consumption Questionnaire (iMTA MCQ) [36]. All significant costs and health effects on the short term up to 4–6 weeks after delivery or termination of pregnancy will be considered. Therefore, these questionnaires will be sent at 20 and 32 weeks GA and 4 weeks after the estimated due date. In case of an intra-uterine fetal demise or termination of pregnancy during the trial, women will be sent specifically adjusted questionnaires.

Participant perspective on the 3D VR ultrasound will be evaluated with an in-house developed questionnaire. This survey includes questions about the value of ultrasound imaging in the first trimester and personal perception of the added value of 3D VR. This questionnaire will be sent after the first trimester 3D VR ultrasound or around 13 weeks GA in the control group. This questionnaire will be validated in a subset of 50 participants.

Ultrasonographer opinion of both the first trimester 2D and the 3D VR ultrasound will be evaluated by another in-house developed questionnaire. More specifically, the additional value of the 3D VR in terms of patient understanding, counseling and detection of anomalies will be examined.

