Recreational drug use during first trimester	No/yes: what drugs; frequency per day?
Folic acid use during and/or prior to pregnancy	No/yes during pregnancy/yes started prior to pregnancy
Pregnant after artificial reproductive technology	No/yes: what type of assisted reproduction
First trimester screening for aneuploidy	No/yes: result
Medication	No/yes: what medication, dosage, starting and stopping date?
Antidepressant	Never/yes currently/yes previous use
**Questionnaires**	**Timing**
Current health status^a^	At inclusion, intervention or 13 weeks’ GA, 20 weeks’ GA, 6 weeks after due date
Anxiety and depression^b^	At inclusion, intervention or 13 weeks’ GA, 20 weeks’ GA, 6 weeks after due date
State and trait anxiety^c^	At inclusion, intervention or 13 weeks’ GA, 20 weeks’ GA, 6 weeks after due date
Current health status by VAS^d^	At inclusion, intervention or 13 weeks’ GA, 20 weeks’ GA, 6 weeks after due date
Medical consumption^e^	At 20 weeks’ GA, 32 weeks’ GA, 6 weeks after due date
Patient satisfaction with 3D VR	At intervention or 13 weeks’ GA, 6 weeks after due date
**Ultrasound**	**Measurements**
At inclusion, 1st trimester	Viability, CRL, multiple pregnancies, location
Intervention: 2D + 3D VR First Trimester Ultrasound, 1st trimester	Fetal anomaly scan using 2D and 3D VR. Growth parameters, detection of anomaly. See supplement A
Advanced fetal anomaly scan, 2nd trimester	Fetal anomaly scan using 2D. Growth parameters, detection of anomaly
**Pregnancy outcome**	**Outcome**
Outcome	Live birth, termination, intra-uterine fetal demise
Mode of delivery	Vaginal / Instrumental delivery / Cesarean section
Gestational age at delivery	Days (mean ± SD)
Invasive testing	No/yes: result
Date of invasive testing	
**Neonatal outcome**	**Outcome**
Birthweight	Birthweight, grams (mean ± SD)
Gender	Male/female
Congenital malformation	No/yes: what malformation
Prenatal diagnosis	Confirmed/discrepancy in findings: postnatal new or other findings

^a^SF-36: MOS 36-item Short Form Health Survey, ^b^HADS: Hospital Anxiety and Depression Scale, ^c^STAI: Spielberger State-Trait Anxiety Inventory, ^d^VAS: visual analogue scale, ^e^iMTA MCQ: iMTA Medical Consumption Questionnaire, CRL: Crown-Rump Length, 2D: two-dimensional, 3D VR: three-dimensional virtual reality

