#### Data-analysis

Data will be analyzed according to the intention-to-treat principle. No interim analysis will be performed.

Statistical analysis will be performed using IBM SPSS (SPSS Inc., Chicago, IL, USA) and R Studio (The R Foundation for Statistical Computing). Descriptive statistics will be used to describe the baseline characteristics of both the control and intervention group (e.g. maternal characteristics such as ethnicity, age, smoking status, Body-Mass Index (BMI) and family history, pregnancy characteristics such as parity and pregnancy outcome, medication use such as antidepressants and antiepileptic medication). Categorical data will be presented by number of participants (%) and numerical data by median (interquartile range). These baseline characteristics will be compared between the arms using Mann Whitney U-test for continuous variables and chi-squared test for categorical variables. When the expected count in 20% or more of the cells of the cross table for the categorical variables is 5 or lower or if any cell is empty an exact test will be used instead. A significance level (alpha) of 0.05 will be used. No multiplicity correction will be applied.

The economic analysis will be performed from the societal perspective. The costs and quality of life will be compared between the two diagnostic regimens. Descriptive statistics will be used to describe the outcomes of quality of life analysis (control arm versus intervention arm).

Ultrasound is considered safe in pregnancy, therefore a data monitoring committee is not required [43]. Yearly reports will be sent to the ethics committee on the progress of the trial. When major modifications to the protocol are made, all people involved will be informed.

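### The second quality-of-life form is timed by the scan in one arm and by gestational age in the other, and entry stays open to the end of the scan window with no stated lead time

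*Protocol article*

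**What the plan says.** All references are to the protocol article.

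- **Entry.** Under Study population, women must be in the "first trimester of pregnancy, up to 14 + 0 weeks" of gestation.
- **Referral.** Under Procedures, recruitment and randomization: "Referring healthcare providers will be contacted to ensure timely referral (< 14 + 0 weeks’ GA". Counselling, written consent, registration and randomisation come after referral.
- **Scan.** Under Intervention group: "The intervention consists of a first trimester 2D and 3D VR ultrasound examination between 11 and 14 weeks GA". The section does not say whether 14+0 itself counts. The Background places the end of the first trimester below 14 weeks.
- **Quality-of-life forms.** Under Questionnaires, the baseline set goes out on the day of inclusion. The second set is timed by "the first trimester 3D VR ultrasound (or after 13 weeks GA for the control group".
- **Participant-perspective form.** In the same section: "This questionnaire will be sent after the first trimester 3D VR ultrasound or around 13 weeks GA in the control group".
- **Table 1**, under Outcome measurements, gives the quality-of-life schedule as "At inclusion, intervention or 13 weeks’ GA, 20 weeks’ GA, 6 weeks after due date".
- **Analysis.** Under Data-analysis: "Data will be analyzed according to the intention-to-treat principle".

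**The concern.** Two features of the timetable interact.

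First, the last day for entry is also the last day (or the day after the last day) for the scan. The article does not ask anyone to confirm, before allocation, that a scan can still be arranged. An intervention woman who misses it receives what the control arm receives but is counted in the intervention arm. That pulls the comparison of detection rates towards no difference.

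Second, the two arms use different clocks for the second form. The intervention arm's clock is an event that can fall at any point in a three-week window. The control arm's clock is a gestational age near the end of that window. Anxiety, wellbeing and health status may well change over these weeks, and time since enrolment may matter too. A between-arm difference at this time point would then mix the effect of the scan with differences in when the women were asked. The QALYs are also derived from the questionnaires, so the economic comparison may take in the same mismatch.

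**Working it through.** There is no stated figure to reproduce; the check is a count of days. Gestational age w+d is taken as 7w + d days.

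**1. Days left for the scan, entry day included.** Formula: last scan day − entry day + 1.

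| Entry | Last scan day 14+0 | Last scan day 13+6 |
|---|---|---|
| 13+0 | 8 | 7 |
| 13+3 | 5 | 4 |
| 13+5 | 3 | 2 |
| 13+6 | 2 | 1 |
| 14+0 | 1 | 0 |

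If 14+0 counts, every eligible entry day leaves at least one day. If the window ends at 13+6, as the Background's definition of the first trimester suggests, only entry on 14+0 leaves none. If 14 weeks were read as running to 14+6, entry on 14+0 would still leave 7 days. The fit is tight at the end, but only one entry day can be incompatible with the scan.

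**2. Can a late control complete the second form?**

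- Read as *after* 13 weeks (Questionnaires): yes on every entry day. No end is stated.
- Read as completed week 13, 13+0 to 13+6 (Table 1): only entry on 14+0 misses it.
- Read as exactly 13+0 (Table 1): the seven entry days from 13+1 to 14+0 miss it.

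What the plan asks of late controls thus depends on which wording is followed.

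**3. Interval from baseline to second form.** For the intervention arm this is (scan day − entry day), with the scan anywhere from the later of 11+0 and entry up to 14+0. For the control arm it is (13+0 − entry day).

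| Entry | Intervention, days | Control at 13+0, days |
|---|---|---|
| 10+0 | 7 to 28 | 21 |
| 12+0 | 0 to 14 | 7 |
| 13+0 | 0 to 7 | 0 |
| 13+3 | 0 to 4 | already 3 days past |

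With 13+6 as the last scan day, each upper end falls by one day. Under *after* 13 weeks, a control entering at 13+3 meets the condition on the day she enrols, so her form may be sent that day or at any later time.

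**4. Gestational age at the second form.** A control measured at 13+0 (day 91) is compared with intervention women measured from 11+0 (day 77) to 14+0 (day 98). That is 91 − 77 = 14 days earlier to 98 − 91 = 7 days later. This mismatch does not depend on late entry and can affect women enrolled at any time.

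**The case against.** The case against is substantial, and much of it stands.

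- *Coinciding limits are not a contradiction.* This is correct. A reader might infer that late entrants cannot follow the plan in either arm. The documents do not support that: the scan remains possible on every entry day except at most 14+0, and the wording under Questionnaires can be met by any late control.
- *Forms due together.* A reader might infer that every control enrolled after 13+0 has both forms due at once. That does not follow, because *after* 13 weeks has no end. It is a possibility that the wording allows, not a certainty.
- *Dilution of the primary comparison.* One could take a share f of intervention women as unscanned, give them the control detection rate, and shrink the planned 70 − 65 = 5 points to 5 × (1 − f): 4.75 points at f = 5%, 4.0 at 20%. The article gives no distribution of gestational age at entry, so no value of f has an anchor. Obstetric care is described as starting at about 8 weeks, with a dating scan around 10 weeks. That points to early contact and a small f.
- *Two limits for one thing.* Up to 14+0 and below 14+0 might be read as conflicting. The first limits eligibility and the second is a target for referral, so they need not match.
- *Short intervals affect both arms.* Late intervention entrants also have few days before their scan, and randomisation should balance gestational age at entry. This answers the concern about late entry as such. It does not answer the different clocks, which apply after allocation and differ by arm.
- *Operational detail and modest stakes.* Booking rules may sit in the full protocol, the flow chart is not shown, and quality of life is secondary and analysed descriptively. These points limit the weight. The arm-specific timing of the form, however, is a rule that the article states, not a missing detail.

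**Conclusion.** The point holds in a limited form. The firm part is that the second quality-of-life form is tied to the scan in the intervention arm and to gestational age in the control arm. The arms are therefore not measured at matched times: up to 14 days apart in one direction and 7 in the other if the control form is sent at 13+0. Controls entering after 13+0 can have almost no interval from baseline. The 13-week time point is also worded in different ways: *after* in the text and plain in Table 1 for the quality-of-life forms, and *around* for the perspective form.

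The weaker part is that entry runs to the end of the scan window with no stated lead time, so a few late intervention women may go unscanned and still be analysed in that arm. The effect on the primary outcome cannot be quantified from the documents and is probably small.

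This rests on reading the timing rules as printed and on there being no further scheduling rule in the documents not shown.

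**What to change.** 1. Before allocation is shown, record for every woman a provisional scan date inside the protocol's existing 11 to 14 week window. If no date is available, she is not randomised. State whether 14+0 belongs to that window. The window itself need not change.
2. Send the second quality-of-life form at the scan in the intervention arm and on the provisional scan date in the control arm. The date is fixed before allocation, so the intended interval and gestational age are the same in both arms.
3. Reconcile the 13-week wording between Questionnaires and Table 1 accordingly, including that for the perspective form.

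The cost is one extra field at randomisation, a changed trigger for the control form, scheduling work for slots released after allocation to control, and the loss of the few women for whom no slot in the window can be found. Rescheduled scans will leave some mismatch, so the actual completion date should be recorded in both arms.
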